In daily practice, speech therapists help document the presence or absence of a range of components required for swallowing in order to guide therapy and monitor its effectiveness by repeated assessment over time. The clinical reality of patients with DOC, mainly the lack of response to simple motor commands (in UWS and MCS–) and functional communication, makes it difficult to fully understand and appropriately treat their swallowing disorders. For these reasons, classical swallowing assessment at the bedside can be unsuitable for this population. There is a lack of appropriate bedside tools to appraise and monitor swallowing disorders in patients with DOC. The impossibility of orienting interventions based on determined quantitative and qualitative swallowing components makes it more difficult to develop a treatment plan and assess the patient's progress.

Our recent DOC cohort study (13) found some links between swallowing and the level of consciousness. In particular, none of the patients with UWS and only a minority of the patients in MCS exhibited an effective oral phase of swallowing (adequate lip prehension, tongue propulsion, and no post-swallowing oral stasis). However, these links are not yet completely understood, and further studies are necessary to increase our knowledge of which components of swallowing are linked to consciousness and to what extent. In this context, the validation of a tool that focuses on qualitative and quantitative swallowing components will help us identify swallowing behaviors that may be considered unequivocal signs of consciousness in patients with DOC. These results may eventually contribute to the development of new diagnostic guidelines for DOC that would include swallowing behaviors in their criteria.

The aim of this article is to present a protocol that develops and validates the SWallowing Assessment in Disorders Of Consciousness (SWADOC). This tool will be administered repeatedly to a population of patients with DOC by different examiners, and intrinsic test characteristics will be calculated. The relationship between patients' level of consciousness and SWADOC scores will also be studied.

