**Figure 1 F1:**
[figure not shown]
Description of the SWADOC. ENT, Ear, Nose, and Throat; SWADOC, SWallowing Assessment in Disorders Of Consciousness.

The “SWADOC-scored” subsection includes eight quantitative items (Figure 2; Supplementary Material 3). Four items are linked to the oral phase and four to the pharyngeal phase. For each quantitative item, patient's abilities are rated on a four-level scale ranging from 0 to 3. These levels correspond to item scores that can be added together to calculate three performance scores: the oral phase subscore (sum of the four oral item scores), the pharyngeal phase subscore (sum of the four pharyngeal item scores), and the total swallowing score (sum of the eight item scores).

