### Study Hypotheses

Our main hypothesis is that the SWADOC is reliable and valid.

Our second hypothesis is that the subscores (oral phase and pharyngeal phase) and the total score are related to the patient's level of consciousness. Moreover, based on previous studies (13, 15), we expect that UWS patients will be at level 0 for oral phase items 1, 3, and 4 of the SWADOC-scored: no mouth opening at spoon approach, no spontaneous lip prehension, and no appropriate tongue propulsion.

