#### Power of the Study

The sample size was calculated using a power calculation (G * Power, Universities of Kiel, Mannheim, and Düsseldorf) in a one-way analysis of variance (ANOVA) with a significance level of 0.05 and a power of 0.8. Effect size is based on previous published data on swallowing performance in patients with DOC (13). Cohen's *d* was used to estimate the effect size; the result was 0.659, corresponding to an eta-squared of 0.0979. We round up and base our calculation on an effect size of 0.1, corresponding to an intermediate effect. In this context, a total sample size of 104 participants (26 per group) is needed to demonstrate a difference in SWADOC‘ subscores and total score between the four consciousness groups. If, by the end of June 2025 the sample size is not reached, we will discuss extending the data collection period if necessary.

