#### Relationship Between Swallowing Components and Levels of Consciousness

The differences in SWADOC-scored items, oral and pharyngeal subscores for the SWADOC-scored, and total score for the SWADOC-scored for the consciousness diagnostic groups will be assessed using a comparison of means with a one-way ANOVA. Violation of the homogeneity of variance will be checked using Levene's test. If this is the case, we will use Welch's approximation instead of an ANOVA. If there is a significant main effect, we will perform Tukey's honestly significant difference (HSD) test to compare all pairwise differences. If there is a severe violation of the normality, we will perform a Kruskal–Wallis test with the Dwass-Steel-Critchlow-Fligner (DSCF) multiple comparison analysis. Partial eta-squared will be used as a measure of effect size. *Post-hoc* multiple comparisons will be conducted to identify where significant differences between consciousness groups exist. SWADOC scores will be the dependent variable, while consciousness group will be the independent variable. Statistical analysis will be performed by a researcher blind to the consciousness category.

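### Tukey HSD is kept as the post-hoc test even after Welch, where its pooled variance is the wrong error term, and no planned test addresses the prediction that UWS patients are at level 0 on oral items 1, 3 and 4

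*Protocol article*

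**What the plan says.** All references are to the protocol article.

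- *Relationship Between Swallowing Components and Levels of Consciousness*: items, the two subscores and the total are compared across UWS, MCS–, MCS+ and EMCS by one-way ANOVA. If Levene's test shows unequal variances, Welch replaces the ANOVA. A significant main effect is followed by Tukey's "honestly significant difference (HSD) test to compare all pairwise differences". No other post-hoc test is named for the Welch route. A severe departure from normality leads to Kruskal–Wallis with DSCF comparisons. The section gives no criterion for severe, and does not say whether the variance check or the normality check decides first.
- *Study Hypotheses*, under the second hypothesis: "we expect that UWS patients will be at level 0 for oral phase items 1, 3, and 4 of the SWADOC-scored".
- *Introduction*, on the purpose: to help "identify swallowing behaviors that may be considered unequivocal signs of consciousness in patients with DOC".
- *Presentation of the Tool*: for each quantitative item, "patient's abilities are rated on a four-level scale ranging from 0 to 3".
- *Power of the Study*: "a total sample size of 104 participants (26 per group) is needed", to show a difference in the subscores and total score.

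**The concern.** There are two separate faults.

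**Error term.** Welch is used because the groups have different variances. Tukey HSD then judges every pair against one pooled variance. Pairs of low-variance groups are held to too wide a yardstick and pairs of high-variance groups to too narrow a one. If UWS patients cluster near the floor, the UWS versus MCS– contrast is the one that loses power, and it is the contrast of most interest for signs of consciousness.

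**Hypothesis without a matching analysis.** The level-0 prediction is a statement about one group: practically no UWS patient scores above 0 on three named items. The analysis named for the items compares groups with each other. A significant result would show that groups differ and could be read as support for a claim it does not test. If the prediction is exactly true for an item, the UWS variance on it is zero and the Welch statistic cannot be computed.

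**Working it through.** **1. The plan's own figure.** Inputs from *Power of the Study*: test "with a significance level of 0.05 and a power of 0.8"; for Cohen's d, "the result was 0.659, corresponding to an eta-squared of 0.0979".
- η² = d²/(d² + 4) = 0.4343/4.4343 = 0.0979, rounded to 0.1.
- f² = 0.1/0.9 = 0.111; λ = 104 × 0.111 = 11.56.
- The noncentral F with 3 and 100 df gives power 0.808. At 100 patients it is 0.790.

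So 104 reproduces. Nothing below changes it.

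**2. Tukey after Welch.** The documents give no SDs. Assume 0.2/0.6/1.0/1.2 for UWS/MCS–/MCS+/EMCS, with 26 per group.
- Pooled variance = (0.04 + 0.36 + 1.00 + 1.44)/4 = 0.71.
- Tukey critical difference, for every pair = q × √(0.71/26) = 3.695 × 0.1653 = 0.611.

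*UWS versus MCS–, true difference 0.5.*
- Actual standard error = √((0.04 + 0.36)/26) = 0.124.
- Tukey: (0.611 − 0.5)/0.124 = 0.89, so power is about 19% by this normal approximation. Simulation (20,000 runs) gives 21%.
- Games–Howell: df = 25 × 0.40²/(0.04² + 0.36²) = 30.5 and q is about 3.84. Critical difference = 3.84 × √(0.40/52) = 0.337. (0.337 − 0.5)/0.124 = −1.31, so power is about 90%. Simulation gives 90%.

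*The two high-variance groups, equal means, other groups truly different.*
- Actual standard error = √((1.00 + 1.44)/26) = 0.306.
- Tukey: 0.611/0.306 = 1.99, a two-sided rate of about 4.6%. Simulation gives about 5%.
- Games–Howell gives 1.0% by simulation. Tukey itself gives 1.1% when all SDs are equal.

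*Milder assumption, SDs 0.5/0.8/1.0/1.2.*
- Pooled variance = (0.25 + 0.64 + 1.00 + 1.44)/4 = 0.8325; Tukey critical difference = 3.695 × √(0.8325/26) = 0.661.
- Standard error for UWS versus MCS– = √(0.89/26) = 0.185.
- Tukey: (0.661 − 0.5)/0.185 = 0.87, power about 19%. Games–Howell: df about 42, q about 3.78, critical difference 0.495, power about 51%.
- High-variance pair under Tukey: 0.661/0.306 = 2.16, a rate of about 3%.

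**3. All means equal.** Tukey runs only after a significant omnibus test. Simulated family-wise error without and with that gate:

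| Assumed SDs | Group sizes | Tukey alone | Welch gate, then Tukey |
|---|---|---|---|
| 0.2/0.6/1.0/1.2 | 26 each | 7.2% | 3.2% |
| 0.5/0.8/1.0/1.2 | 26 each | 6.1% | 3.3% |
| 0.5/0.8/1.0/1.2 | 35/29/24/16 | 11.0% | 4.3% |

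**4. The level-0 prediction.** F, Welch and Kruskal–Wallis depend only on differences, or on ranks, between groups. Add 1 to every patient's item score, so that all UWS patients sit at level 1, and each statistic is unchanged. None of them can tell level 0 from level 1.

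The question is answered by a proportion. If 26 of 26 UWS patients are at level 0, the exact two-sided 95% lower limit is 0.025^(1/26) = 0.868. Up to 13.2% of UWS patients could still score above 0.

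**5. Welch with a constant group.** Welch weights each group by n/s². With s² = 0 for UWS the weight is infinite, and the statistic, df and p-value are undefined. One UWS patient scoring 1 makes it computable. If 5% of UWS patients truly score above 0, all 26 score 0 with probability 0.95^26 = 26%.

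For simulated items with UWS all at 0 and levels 0/1/2/3 assumed at 70/20/7/3% in MCS–, 50/25/15/10% in MCS+ and 30/30/20/20% in EMCS:
- Levene's test and a Shapiro test on residuals both rejected in every run, so both branches are triggered at once.
- Kruskal–Wallis and DSCF could be computed. DSCF found UWS versus MCS– in 84% of runs, Tukey in 9%.

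**The case against.** The plan already names a rank-based route in the same section. A 0–3 item on which a whole group is constant is severely non-normal on any sensible reading, so items 1, 3 and 4 would most naturally go to Kruskal–Wallis with DSCF, where neither the Welch nor the Tukey problem arises. This largely stands. What remains is that severe has no criterion and the order of the branches is not fixed, while such data also trip Levene's test.

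A reader might infer that the whole ANOVA–Welch–Tukey path breaks down if the prediction is right. The documents do not support that. The prediction covers three of eight items. The oral subscore can still vary through item 2, and no floor is predicted for the pharyngeal subscore or the total. Welch is normally computable for those scores, which are the ones used for the sample size.

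A reader might also infer that Tukey after Welch inflates family-wise error, from figures such as 7.2% or 11.0%. Those ignore the omnibus gate that the plan sets. With it, error under equal means stays below 5%. The gate gives no protection once some groups truly differ, which is what the plan expects, so the per-pair error and the power loss stand.

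The SDs are assumed, and a sixfold ratio looks more like item data than subscores. That is fair, and is why the milder case is shown.

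Finally, the level-0 statement is an expectation under the second hypothesis, and reporting a proportion with an interval could be left to an analysis plan that is not at hand. That lowers the weight of this part. But the protocol does name the analysis for the items, and that analysis does not answer the stated prediction.

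**Conclusion.** The point holds in two limited parts.

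1. Tukey HSD is the wrong post-hoc test wherever Welch has been used: for the subscores, the total and any item kept on the parametric path. The direction follows from the method; the size depends on assumed SDs. Power for a UWS versus MCS– difference of 0.5 is about 21% against 90% under a strong variance gradient, and about 19% against 51% under a milder one. The per-pair false-positive rate for the high-variance pair is about 5% or 3%, against about 1% intended, when other groups differ. Overall false-positive control with all means equal is not at issue.
2. The level-0 prediction for items 1, 3 and 4 has no matching analysis. The undefined Welch statistic is a narrow risk: it needs every UWS patient at 0 on an item and that item left on the parametric path.

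This concerns an analysis under the second hypothesis. It does not touch the main hypothesis of reliability and validity or the 104 patients. It should be fixed before analysis, but it does not undermine the study.

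**What to change.** - For the subscores and total: follow Welch with Games–Howell, and keep Tukey HSD only where the equal-variance ANOVA was used.
- For the eight 0–3 items: use Kruskal–Wallis with DSCF, already named in the plan, from the outset. This removes the undefined Welch case and the need to judge severity or branch order for items.
- For the level-0 prediction: report, for each of oral items 1, 3 and 4, the proportion of UWS patients at level 0 with an exact 95% interval, and judge the prediction on that. State how the three sessions count, for example at level 0 in every session, so that each patient enters once.

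The cost is a change of wording; all methods are in standard software. Games–Howell loses a little power if variances are in fact equal: with 26 per group its df fall from 100 to about 50 and q rises from 3.695 to about 3.76, a critical difference about 2% wider. No extra patients or assessments are needed.

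### Partial eta-squared, the only effect size named, runs 0.026 to 0.029 too high for medium to absent links with consciousness on the ANOVA path; a nearly unbiased measure costs one sentence

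*Protocol article*

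**What the plan says.** In the Protocol article, under Relationship Between Swallowing Components and Levels of Consciousness, group differences in the SWADOC-scored items, the two subscores and the total "will be assessed using a comparison of means with a one-way ANOVA". Two departures follow. For unequal variances: "If this is the case, we will use Welch's approximation instead of an ANOVA". For non-normal data: "If there is a severe violation of the normality, we will perform a Kruskal–Wallis test", with the DSCF procedure for pairwise comparisons. One general sentence then names the effect size: "Partial eta-squared will be used as a measure of effect size". It is not tied to a test path, and the article names no alternative.

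The planning effect, under Power of the Study, is on the same scale. A Cohen's d was estimated from earlier data, and "the result was 0.659, corresponding to an eta-squared of 0.0979". The text continues "We round up and base our calculation on an effect size of 0.1", and concludes that "a total sample size of 104 participants (26 per group) is needed".

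**The concern.** Chance differences between group means add to the between-group sum of squares, so eta-squared exceeds the population value on average. In relative terms the excess is largest where the true link is weak. The article's second aim is the relation between consciousness and SWADOC items and scores, and the Introduction asks both which swallowing components are linked to consciousness and how strongly. An estimator that lifts unrelated and weakly related items by nearly 0.03 blurs that contrast.

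A smaller matter is that the article matches the post-hoc procedure to the test (Tukey with ANOVA, DSCF with Kruskal–Wallis) but does not do so for the effect size. Under Study Hypotheses it expects patients with UWS to score 0 on oral items 1, 3 and 4. One group would then have almost no variance, so at least for those three items the ordinary ANOVA may not be the test that is used.

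**Working it through.** **Inputs.** k = 4 groups and N = 104, 26 per group (Population and Recruitment; Power of the Study); d = 0.659, eta-squared 0.0979, rounded to 0.1 (Power of the Study); a test "with a significance level of 0.05 and a power of 0.8".

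**The plan's own figures.**
- Eta-squared from d: d²/(d² + 4) = 0.4343/4.4343 = 0.0979, as stated.
- Sample size: f = √(0.1/0.9) = 0.333 and λ = N·f². The noncentral F gives power 0.808 at N = 104, the smallest N with equal groups that reaches 0.80. The stated 104 reproduces.

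**Bias with no effect.** The expectation of eta-squared is exactly (k−1)/(N−1) = 3/103 = 0.029. About 10% of null results exceed 0.06.

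**Bias with an effect.** One million simulated ANOVAs per true value, normal with equal variances, k = 4, N = 104:

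| True value | Mean eta-squared | Bias | Relative excess | Bias of omega-squared |
|---|---|---|---|---|
| 0 | 0.0291 | +0.029 | – | 0.000 |
| 0.05 | 0.0773 | +0.027 | 55% | −0.001 |
| 0.0979 | 0.1234 | +0.026 | 26% | −0.002 |
| 0.2 | 0.2224 | +0.022 | 11% | −0.003 |
| 0.3 | 0.3195 | +0.020 | 7% | −0.003 |
| 0.5 | 0.5146 | +0.015 | 3% | −0.002 |

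Over the same range epsilon-squared is biased by between 0 and −0.001.

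**Is the correction paid for in variance?** Hardly. At 0.0979 the standard deviation is about 0.057 for omega-squared and 0.056 for eta-squared. Root mean squared error is √(0.057² + 0.0016²) = 0.057 for omega-squared and √(0.056² + 0.0255²) = 0.062 for eta-squared.

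**What a reader would see.** For an observed eta-squared of 0.10, F = (0.10/0.90)(100/3) = 3.70. Then omega-squared = 3(F−1)/[3(F−1) + 104] = 8.11/112.11 = 0.072, and epsilon-squared = 0.10 − 0.90 × 3/100 = 0.073.

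**Kruskal–Wallis path.** Eta-squared computed on ranks is H/(N−1). Applying the epsilon adjustment, η² − (1−η²)(k−1)/(N−k), gives [(N−1)η² − (k−1)]/(N−k) = (H−k+1)/(N−k). The rank counterpart therefore belongs to the same family and carries the same type of correction.

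**Welch path.** The documents give no group means or standard deviations, so any figure rests on assumptions. With assumed means of 0, 0.3, 0.6 and 0.9 and standard deviations of 0.5, 0.8, 1.2 and 1.5, sums-of-squares eta-squared was biased by +0.026 with equal groups, and by +0.036 or +0.020 with groups of 40/30/20/14 or 14/20/30/40. Omega-squared was biased by −0.001, +0.009 and −0.008 in the same three settings. These figures are illustrations only.

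**The case against.** The strongest reply is that eta-squared is a conventional descriptive measure, can be reported beside any test, and is the metric of the planning effect. The main hypothesis concerns reliability and validity; the link with consciousness comes second. Significance is judged at p < 0.05, and changes to the scale depend on agreement and on floor or ceiling effects, not on an observed effect size. All of this stands, and it is why the point is minor. A condensed article may also leave effect-size details for each test path to the full protocol. That too stands, so the lack of path-specific measures is not itself a fault. The named estimator is nevertheless a stated choice, and its bias can be avoided.

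A reader might infer three stronger claims that the documents do not support:
- *All links are overstated by 0.03.* The bias is near 0.03 only for small effects and about half that at 0.5.
- *The 0.03 arises because the measure does not match Welch or Kruskal–Wallis.* It is purely sampling bias in the ANOVA setting. The eta-squared family extends to ranks, and the article does not say that the measure would be derived from a Welch F.
- *The observed values will be judged against 0.1.* That value serves only the sample size; no such comparison is planned.

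A further objection is that using a different kind of measure on each path, such as pairwise mean differences for Welch, would prevent comparison across components. This is right, and the change proposed here respects it.

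**Conclusion.** The point holds as a low-cost improvement. On the ANOVA path the only named effect size is biased upwards by 0.029 at no effect, about 0.026 at the planning effect of 0.098, and 0.020 or less from 0.3 upwards. The figures assume normal data, equal variances and the planned four groups of 26. Nothing firm can be said about the size of the bias on the other two paths. Omega-squared or epsilon-squared removes nearly all of the bias on the ANOVA path, with slightly lower total error at the planning effect. P-values, power, sample size and every stated decision are unchanged.

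**What to change.** Replace the effect-size sentence by:

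> Omega-squared (or epsilon-squared) with a 95% CI will be used as the effect size; where the Kruskal–Wallis test is used, its bias-adjusted rank counterpart (H−k+1)/(N−k) with a bootstrap CI will be reported.

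If Welch is used, keep the same variance-explained measure with a bootstrap interval, and give Welch-based mean differences only as an addition. Choose omega- or epsilon-squared before the analysis and use the same one for every item, subscore and total.

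The cost is one sentence and no new data. Reported effect sizes become slightly smaller and can be slightly negative near zero, which should be explained where they are reported. With unequal variances and unequal group sizes the adjusted measure is no longer exactly centred, which is one more reason to show its interval.

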### Population and Recruitment

This study will be carried out in patients with DOC or emerging from DOC following severe acquired brain injury. Patients will be divided into four groups according to their clinical diagnosis, as assessed with the SECONDs and with the CRS-R: UWS, MCS–, MCS+, and EMCS. Participants will be recruited from inpatient neurological rehabilitation programs in post-coma units and rehabilitation services or among patients hospitalized for a multimodal assessment of consciousness for diagnostic and prognostic purposes.

Only patients who meet all of the following inclusion criteria will be considered for enrollment: (1) age above 18 years; (2) perfect knowledge of French language before the injury; (3) previous coma phase caused by a severe acquired brain injury; (4) medical stability (no mechanical ventilation or sedation, no acute medical pathology such as infection or respiratory distress); (5) no neurological or otorhinolaryngological disease that can impact swallowing prior to the brain injury; (6) minimum of 28 days since the acquired brain injury at inclusion (28, 29); (7) diagnosis of UWS, MCS–, MCS+, or EMCS based on the SECONDs and the CRS-R; (8) informed consent from the patient's legal representative; and (9) affiliated patient or beneficiary of a health insurance plan (for participants in France only).

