### Validation of the Study Procedure

Each patient enrolled in the validation study will have his or her level of consciousness assessed at baseline with a single administration of the CRS-R. Next, the level of consciousness and swallowing abilities will be assessed with three tools during three separate sessions (only one administration of the FOTT-SAS) in the morning or the afternoon in order to assess the tool's intrarater and interrater reliability. The baseline assessment and sessions will be spread over 5 consecutive days.

CRS-R: This is a standardized neurobehavioral assessment of consciousness composed of six subscales (auditory, visual, motor, oromotor/verbal, communication, and arousal). It assesses different functions with various numbers of hierarchically arranged items that distinguish UWS, MCS, and EMCS patients. The total score is composed of the sum of the maximum scores obtained in each subscale.SECONDs: It is shorter to administer (median of 7 min) and requires only a mirror as material. It consists of eight items: observation and reporting of spontaneous behaviors, response to command, communication, visual pursuit and fixation, pain localization, oriented behaviors, and arousal. We have chosen this consciousness tool during sessions rather than the CRS-R because of its short duration so that the SWADOC can be administered immediately before or after, given that attentional abilities are often reduced in patients with DOC. The SECONDs provides a total score directly reflecting one diagnosis (0 = coma; 1 = UWS; 2–5 = MCS–; 6–7 = MCS+; 8 = EMCS).SWADOC: This tool includes a battery of 56 quantitative and qualitative items. Quantitative items are grouped in the SWADOC-scored, with oral and pharyngeal subscores and a total score. Running the whole SWADOC lasts between 15 and 25 min based on preliminary tests.FOTT-SAS: The results of the SWADOC-scored in one session will be compared to those of the FOTT Swallowing Assessment of Saliva (FOTT-SAS) (30). The test comprises seven questions; if items 1–4 are answered “Yes” and items 5–7 are answered “No,” oral intake should be initiated (Supplementary Material 4). The FOTT-SAS includes items that can be scored based on the administration of the SWADOC. In that respect, no additional administration will be required.

The clinical protocol procedure is illustrated in Figure 3.

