**Figure 3 F3:**
[figure not shown]
Study protocol. Example of the assessment program for a patient. The program for each patient is organized such that the three sessions take place over 5 days in the morning or in the afternoon. The SECONDs is administered before or after the SWADOC. Examiner 2 will administer the SWADOC before or after examiner 1 in one of the three sessions. Examiner 1 will score the FOTT-SAS after one of the three sessions. SECONDs, Simplified Evaluation of CONsciousness Disorders; SWADOC, SWallowing Assessment in Disorders Of Consciousness; FOTT-SAS, Facial Oral Tract Therapy Swallowing Assessment of Saliva.

Because of clinical realities, no attempt will be made beforehand to standardize the order (SECONDs before or after SWADOC and examiner 2 before or after examiner 1) or time of day (morning or afternoon) of evaluations. However, during data collection, efforts will progressively be made to balance the order and time of day and the time of evaluation of examiner 2 (before or after examiner 1).

The administration of the SWADOC at each session will allow us to assess the tool's intrarater reliability (temporal stability). Directly before or after one of the three sessions, a second examiner will administer the SWADOC a second time to test its interrater reliability. The second assessment will be blinded to the results of the first. To be able to take into account potential mismatches between the ratings of the two examiners, each scoring protocol will be analyzed directly after the interrater session and a discussion will follow to try to understand the reasons for any discrepancies. This information will be noted in the protocol. After the recruitment procedure and depending on the degree of agreement based on the statistical analysis, modifications of the instructions, and/or items will be considered based on the qualitative information collected from the examiners.

Sensitivity to change will determine whether changes in the level of consciousness (variations in SECONDs scores) result in changes in the SWADOC-scored across the three assessments of the same patient. Repeating the SECONDs assessment will also allow for a reliable assessment of the patient's level of consciousness (UWS, MCS–, MCS+, or EMCS) and decrease the risk of misdiagnosis (31).

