### Limitations and Pitfalls

There are a number of limitations on this study especially because of the clinical challenges of dealing with patients with DOC. The main limitation is the feasibility of having each patient undergo a baseline administration of the CRS-R and three assessments. This group's arousal fluctuates considerably, as they are highly sensitive to stress and fatigue, and often subject to medical complications (e.g., vomiting, pain, respiratory infections, etc.) that may limit their availability to participate in the study. To take into account this pitfall of the application of the methodology to patients with DOC, we chose to extend the evaluation period to five days rather than two days as initially planned.

Although, we have developed the most accurate levels possible for each item and a complete scoring guide, the SWADOC is based on subjective observations of swallowing components. The interrater reliability will help us determine the consistency of the rating system between examiners. Depending on these results, the scale may be adapted.

Furthermore, the decision to assess the level of consciousness using the SECONDs may seem questionable because this scale is recent, but it is derived from the CRS-R, which is known to be the gold standard scale for behavioral assessment of consciousness. Nevertheless, the SECONDs is much quicker to administer and includes the five CRS-R items that detect 99% of MCS patients (12). Moreover, this scale has good intra- and inter-rater reliability (kappas ranging from 0.85 to 0.91 and 0.82 to 0.85, respectively). However, we considered adding one administration of the CRS-R at baseline before the three sessions because the CRS-R gives more details and precision on the patient's overall state, including reflexes.

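### The article describes no blinding of SWADOC raters to the consciousness results that define the groups, so knowledge of the diagnosis could inflate the group differences of the second hypothesis

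*Protocol article*

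**What the plan says.** The protocol article makes two statements about blinding.

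- On the group comparison (Relationship Between Swallowing Components and Levels of Consciousness): "Statistical analysis will be performed by a researcher blind to the consciousness category".
- On the interrater session (Validation of the Study Procedure, text with Figure 3): "The second assessment will be blinded to the results of the first". This serves interrater reliability and does not concern consciousness level.

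On the grouping variable, Population and Recruitment says: "Patients will be divided into four groups according to their clinical diagnosis, as assessed with the SECONDs and with the CRS-R". The CRS-R is given once at baseline, before the SWADOC sessions. Within sessions, "The SECONDs is administered before or after the SWADOC". The SECONDs was chosen for its short duration, "so that the SWADOC can be administered immediately before or after". On sequence, "no attempt will be made beforehand to standardize the order (SECONDs before or after SWADOC"; balance is only worked towards as data accrue.

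On the outcome, Limitations and Pitfalls concedes that "the SWADOC is based on subjective observations of swallowing components", despite defined levels and a scoring guide, and offers interrater reliability as the check. Study Hypotheses gives the expected direction: UWS patients at the lowest level on oral items 1, 3 and 4.

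**The concern.** The group comparison relates an observer-rated score to a diagnosis obtained in the same patients over the same five days. If the rater knows the diagnosis, that knowledge can influence the score. The explanatory variable then partly determines the outcome.

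The two safeguards in the text do not address this. Blinding the analyst protects choices made during analysis, but it cannot remove bias already in the recorded scores. Agreement between examiners does not help either: two raters who both know the diagnosis can lean the same way, agree closely and both be biased.

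At stake is the second hypothesis, which is also the comparison that sets the sample size. The Introduction hopes that the tool will help identify swallowing behaviours that signal consciousness and may eventually inform diagnostic criteria. An estimate inflated by knowledge of the diagnosis would be a weak basis for that.

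**Working it through.** **1. Who may know what, according to the text**

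| Person | Described as blind to | Described as blind to CRS-R or SECONDs result? |
|---|---|---|
| Analyst | consciousness category | yes |
| Examiner 1 | nothing stated | no |
| Examiner 2 | examiner 1's SWADOC result | no |

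The article does not assign the CRS-R or SECONDs to a person other than the SWADOC rater, and does not say that the diagnosis is withheld from the rater.

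**2. The plan's own figure**

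Inputs from Power of the Study: four groups, alpha 0.05, power 0.8, effect size 0.1 read as eta-squared, total 104 (26 per group).

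- f² = 0.1 / (1 − 0.1) = 0.1111, so f = 0.333.
- Noncentrality = N × f² = 104 × 0.1111 = 11.56.
- The noncentral F distribution with 3 and 100 degrees of freedom gives power 0.808, and 104 is the smallest balanced total that reaches 0.80.

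The stated sample size is reproduced, and the concern does not affect it.

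**3. What a rating shift would do to the same test**

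Assume no true difference, 26 per group, and scores shifted by s within-group SD because the rater knows the group. The documents give no value for s, so a range is shown.

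UWS alone scored s SD lower: group means are (−s, 0, 0, 0) and their variance is f² = 3s²/16.

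| s | f² | 104 × f² | Probability of p < 0.05 |
|---|---|---|---|
| 0.1 | 0.0019 | 0.20 | 0.06 |
| 0.2 | 0.0075 | 0.78 | 0.10 |
| 0.3 | 0.0169 | 1.76 | 0.17 |
| 0.5 | 0.0469 | 4.88 | 0.42 |
| 0.8 | 0.1200 | 12.48 | 0.84 |

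Shift rising linearly from UWS to EMCS over a total span of s SD: f² = 5s²/36.

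| s | f² | 104 × f² | Probability of p < 0.05 |
|---|---|---|---|
| 0.2 | 0.0056 | 0.58 | 0.09 |
| 0.5 | 0.0347 | 3.61 | 0.31 |
| 0.8 | 0.0889 | 9.24 | 0.71 |

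For scale, a UWS-only shift of 0.8 SD induces an eta-squared of 0.12 / 1.12 = 0.107, about the planned effect of 0.1. A shift of 0.2 SD induces 0.0075 / 1.0075 = 0.007.

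**4. Whether examiner 2's scores can carry a check**

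Examiner 2 rates each patient once. If all 104 patients have that rating, the analysis has one score per patient and 26 per group. That is the same layout as in step 2, so power at the planned effect is again 0.808.

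**The case against.** **Silence in a condensed article.** The article does not say who gives the SECONDs, Figure 3 is not shown, and the administration guide and supplements are not at hand. A reader might infer that the same person gives both tests, or that nothing in the study shields the rater. The documents support neither. They support only that the article addresses blinding for this comparison, places it on the analyst, and describes none for the rater.

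**Only the statistician is blinded.** This is true for consciousness level but not in general, because examiner 2 is blinded to examiner 1's result.

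**Raters hold the expectation.** The prediction for UWS patients is the study's hypothesis. No text says that the raters share it or were told of it.

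**Expectation alone could create the link.** The calculation shows this is possible, but only under an assumed absence of any true difference and an assumed shift. Small shifts do little: 0.2 SD in UWS alone gives about 10% rejection. The Introduction reports that no UWS patient in the previous cohort had an effective oral phase, which makes some true difference likely. The realistic concern is an inflated effect, not a wholly false one. Each scored item also has four defined levels and a scoring guide, which limit discretion.

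**Full blinding is unattainable.** This stands. The SWADOC contains command-following items built on SECONDs principles, so any rater sees signs of consciousness while scoring.

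**Scope.** The point touches the second hypothesis. The main hypothesis is reliability and validity, and the diagnostic use of swallowing signs is a later prospect.

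These objections limit how strongly the point can be put. None of them supplies a safeguard against rater knowledge in the group comparison.

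**Conclusion.** The point holds as a risk of inflation. As described, the analyst is the only person blind to consciousness category, and SWADOC raters are not kept from the results that define the groups. The scale is acknowledged to be subjective, so the differences under the second hypothesis may be overstated. Neither analyst blinding nor a high kappa would reveal it.

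The size is unknown. Under an assumed null with 26 per group, rejection rises from 5% to about 10% for a shift of 0.2 SD in UWS alone, and to about 42% for 0.5 SD. These figures rest on assumed shifts, normal-theory one-way ANOVA and equal groups. They do not show that bias is present, and they do not support a claim that the link is an artefact. The sample size of 104 is unaffected. This is a worthwhile, inexpensive improvement.

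**What to change.** 1. Where feasible, do not give examiner 2 the CRS-R and SECONDs results. Record examiner 2's scores as final before the discussion of discrepancies.
2. Pre-state a sensitivity analysis that repeats the group comparison on examiner 2's scores, one per patient. Report it beside the main result, not as a condition for claiming the link, because examiner 2's blinding is only partial.
3. State as a limitation that examiner 1 may know the diagnosis, and that the scale's own command-following items rule out full blinding.

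Do not impose a fixed order with the SWADOC always before the SECONDs. That would place the test that helps define the groups after a 15 to 25 minute assessment, in patients whom the article describes as easily fatigued and limited in attention. The baseline CRS-R and earlier SECONDs results might still be known to the rater.

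Cost: a small coordination burden, one procedural sentence, one extra analysis and one limitation statement. No additional examiner or assessment is needed. The gain is smaller where examiner 2 belongs to the treating team and already knows the diagnosis; the article does not say how often that will be so.
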